## Abstract

The connection between imbalances in the human gut microbiota, known as dysbiosis, and various diseases has been well established. Current techniques for sampling the small intestine are both invasive for patients and costly for healthcare facilities. Most studies on human gut microbiome are conducted using faecal samples, which do not accurately represent the microbiome in the upper intestinal tract. A pilot clinical investigation, registered as NCT05477069 and sponsored by the Grenoble Alpes University Hospital, is currently underway to evaluate a novel ingestible medical device (MD) designed for collecting small intestinal liquids by Pelican Health. This study is interventional and monocentric, involving 15 healthy volunteers. The primary objective of the study is to establish the safety and the performance of the MD when used on healthy volunteers. Secondary objectives include assessing the device’s performance and demonstrating the difference between the retrieved sample from the MD and the corresponding faecal sample. Multi-omics analysis will be performed, including metagenomics, metabolomics, and culturomics. We anticipate that the MD will prove to be safe without any reported adverse effects, and we collected samples suitable for the proposed omics analyses in order to demonstrate the functionality of the MD and the clinical potential of the intestinal content.

## 1. Introduction

The human gastrointestinal tract (GIT) consists of various segments, each characterised by distinct environmental conditions. These environmental conditions play a direct role in shaping the microbiome of the GIT. The gut microbiome, a complex ecosystem, encompasses communities of microorganisms, including bacteria, fungi, and archaea, along with their biological components like metabolites, proteins, or free nucleic acids [1]. The human gut microbiome exhibits a stratified distribution from the duodenum to the colon, characterised by a progressive increase in bacterial density and diversity (from 10^3^ CFU/mL to 10^11^ CFU/mL) along this continuum [2]. It is well established that the human gut microbiome plays a crucial role in preserving the host’s health, directly influencing metabolic and immune homeostasis. Gut microbiome dysbiosis is characterised by a decrease in microbial diversity, the absence of beneficial microorganisms, and the potential presence of pathogenic microbes, and it can lead to alterations in the composition of gut microbiota-derived metabolites, thereby contributing to the development of various pathologies [3,4]. Numerous studies have established connections between the intestinal microbiome and conditions such as metabolic diseases, inflammatory bowel diseases, cancers, and neurological disorders [5,6,7,8,9,10]. Gut microbes exert a direct or indirect influence on the host’s physiology by regulating various hormones, neurotransmitters, or metabolites [11]. Certain metabolites, like Short Chain Fatty Acids (SCFA), are known to have direct impacts on gut physiology, exhibiting anti-inflammatory effects, maintaining the integrity of the gut barrier, and serving as the primary energy source for colonocytes [12,13,14]. These metabolites are either directly produced by gut microbes, from diet, from host metabolite such as amino-acids conjugated bile acids, or de novo [4].

The human gut microbiome has been mainly characterised based on the analysis of faecal samples through the cultivation of gut microbes and DNA based next-generation sequencing [15]. However, these samples do not represent the intestinal microbiome [16]. The faecal microbiome is dominated by four phyla: *Bacillota*, *Bacteroidota*, *Actinomycetota*, and *Pseudomonadota* [17] and has been extensively studied. The upper intestinal tract (the small intestine) is less characterised since its accessibility is limited, and it is known to be less diverse than the faecal microbiome and dominated by the genera *Lactobacillus*, *Clostridium*, *Streptococcus*, *Staphylococcus*, *Veillonella*, and *Bacteroides* [18,19,20,21,22]. The gut microbiome’s composition of the small intestine is strongly influenced by the short transit time of ingested food, the pH and oxygen gradients, as well as enzymes and bile acids produced by the host [14,20]. Studies that aimed to characterise the small intestine employed different collection and analytical methods, thus making comparisons between studies difficult.

Microbiome sampling plays a pivotal role in clinical investigations, aiding in the understanding of gut microbiome dynamics and their implications for human health. To date, various methods for gut microbiome sampling are available, but most of them are invasive for patients and costly for health care facilities. Endoscopic aspiration, while prone to contamination [23], is essential for diagnosing conditions like small intestinal bacterial overgrowth (SIBO) [24]. Luminal brushing offers precision and minimizes contamination but may require time and effort [25]. Surgery, which is non-susceptible to contamination, theoretically provides the most representative samples, yet necessitates preoperative preparations that can disrupt the microbiome [26]. In vivo models, such as ileostomy effluent, offer convenience and insight into diet-microbiota interactions but may not fully replicate the microbiome of individuals with normal anatomy [27]. While these approaches have made significant contributions to clinical research, the invasive nature of surgery and the difficulties associated with obtaining samples from healthy controls constrain their broad utilization. The choice of sampling method in clinical settings should consider the specific research goals and practical constraints while aiming to strike a balance between accuracy and invasiveness. Tang et al. have detailed different approaches currently used for sampling the gut microbiome such as endoscopy or biopsy [28]. To date, some research teams have developed non-invasive methods to sense and collect intestinal liquid by using smart capsules [29].

### 1.1. Rationale

The gastrointestinal tract is a complex ensemble of organs performing a variety of crucial functions in the digestion, absorption, and processing of food and nutrients, as well as in the regulation of the immune system and overall health [30]. Exploring the gastrointestinal tract is essential to gain a deeper understanding of its intricate workings and the profound impact it has on human health, paving the way for more effective diagnostics, treatments, and preventive measures for a wide range of gastrointestinal and systemic diseases [31]. The development of advanced instruments, like endoscopes, in the 19th and 20th centuries, allowed for the direct visualization and exploration of the gastrointestinal tract. Endoscopy, with its various forms such as gastroscopy and colonoscopy, revolutionized the field of gastrointestinal medicine and diagnostics. Even though the technique is minimally invasive, it still requires a medical environment and a clinician, and it is not well accepted by patients due to the great discomfort it causes. Moreover, endoscopy does not allow us to reach parts of the small intestine. To circumvent some of these disadvantages, ingestible devices were developed. Besides the exception of the “Heidelberg capsule” in 1957 for pH measurements [32], smart wireless capsules have been entering the market since 2001, with the PillCam (Given Imaging) imaging video capsule for imaging the gastrointestinal tract [33]. Since then, various other ingestible medical devices have been developed for different purposes, including smart pills for drug delivery and monitoring [34,35]. These devices have significantly advanced medical diagnostics and treatments for gastrointestinal and other related health issues [36,37]. To date, wireless capsule endoscopy is the gold standard for the diagnosis of different small intestinal diseases such as Crohn disease, angiodysplasia, or polyposis [38]. Because a lot of biophysical processes happen in the intestine and since it hosts billions of microorganisms known as the microbiota, sampling the intestinal content has become of great interest [31,39]. Following the trend of ingestible medical devices, multiple devices have been developed to perform sampling, including the Intellicap^®^ [35]. This smart pill was a sophisticated programmable capsule that obtained a CE marking. Since then, other projects have emerged as reviewed elsewhere (Rehan et al., [29]). To sample the human microbiome in a non-invasive way and in vivo, Pelican Health has developed an ingestible device that contains no electronics and that has the unique ability to collect three samples at a time. This article details the clinical protocol used to evaluate the Pelican Health medical device on healthy volunteers for the first time.

### 1.2. Medical Device Description

The Medical Device (MD) is developed to specifically target the small intestine, and it is designed to be easily recovered from faeces. It is a porous polymer protected by two walls. The outermost layer is gastro-resistant, in the form of a size 00 gastro-resistant pharmaceutical capsule. This capsule is produced by Lonza Capsules & Health Ingredients (Colmar, France) and targets the distal parts of the small intestine [40]. This enables the capsule to pass through the stomach without being damaged. The outer wall (capsule) then degrades once it reaches the distal jejunum/proximal ileum. The MD contains tree modules, allowing for the multi-sampling of the small intestinal liquid. These modules are radio-opaque, allowing for the location of the MD in the GIT, if needed, using an X-ray or a scanner. The device is designed in compliance with medical device design standards, using biocompatible, certified materials and has no electronic materials or energy sources, thus limiting production risks and costs. 

### 1.3. Aims and Objectives

The primary objective of this clinical study is to demonstrate the safety and performance of the medical device. This objective is, thus, composite and will be achieved if both the safety and the performance of the MD are observed for at least 12 out of 15 volunteers. 

Each volunteer will ingest only one pill (the MD) containing tree modules.

The secondary objectives of this study are as follows: (1) to verify the safety of use of the MD for the collection of intestinal content, (2) to verify that the MD is transiting in the human intestinal tract, (3) to evaluate the capture of intestinal liquid by the MD, (4) to verify that the MD opened in the intestine, (5) to verify the state of the MD after collection, (6) to evaluate the sample’s functional potential and identify biomarkers (microorganisms, metabolites) via metagenomics and metabolomics, (7) to estimate the volunteer’s experiences about the MD ingestion and its use, and (8) to obtain the sample’s functional potential and identify biomarkers via culturomics for two subjects.

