### 1.4. Primary Outcomes

Safety will be assessed in a binary manner as the absence of the occurrence of adverse events of grade ≥3 with a proven or reasonably conceivable causal relationship with the MD or its related procedure. Grades will be determined using the common terminology criteria for adverse events (CTCAE) classification version 5 (or 6 if available) [41]. 

Performance will be considered satisfactory if at least one of the three modules is analysable. A module will be considered analysable if (1) it is found in the faeces within a 96-h period, (2) the recovered volume of its contents is ≥25 µL, and (3) its visual condition is satisfactory (no faecal contamination).

The criteria to evaluate the secondary objectives are as follows: (1) the number and grade of adverse events notified (including response to follow-up volunteer-diaries, number of unscheduled medical visits); (2) the number of modules recovered per volunteer; (3) the volume recovered from each module (recovered volume must be ≥25 μL); (4) the pH of the recovered MD contents (a measured pH ≥5 will prove that the MD did not sample stomachal liquid where the pH is lower [42]); (5) the visual assessment of the module evaluating whether it is intact and has no visible cracks or damages that could lead to faecal contamination; (6) metabolomic and metagenomic analyses of the module contents; (7) the rating of the device (devices “acceptability”) based on the questionnaire and the end-of-participation visit with the principal investigator; and (8) the results of the culturomic analysis of the module contents, on up to two volunteers.

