### 2.7. Sample Size

The number of subjects to be included is set at 15 healthy volunteers to meet practical feasibility requirements. Any patient whose data are deemed unusable, notably due to sample transport lasting >4 h, will be replaced to obtain 15 usable samples, up to a limit of 20 patients in total.

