### 2.8. Statistical Analysis

Categorical variables will be presented using counts and frequencies, while continuous variables will be presented using mean, standard deviation, median, and interquartile range. Statistical significance will be declared when *p* < 0.05, without adjustment for multiple testing. Any comparisons between groups will be made using non-parametric tests, given the small sample size: Fisher’s tests for qualitative variables and Wilcoxon’s tests for quantitative data. Analyses will be performed using R (version ≥4.2). The normality of continuous variables will be assessed graphically. No replacements of missing data will be performed.

The main objective of the study will be achieved if the safety and performance sub-criteria are met for at least 12 out of the 15 volunteers. All secondary objectives will be analysed using descriptive tools except multi-omics analyses. 

A security interim analysis will be performed after the inclusion of the 3rd volunteer. This will focus strictly on the safety component of the primary outcome. No adjustments for alpha risk inflation are planned.

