We predict that the medical device will be fully safe for the 15 volunteers and that no side-effects will be noticed. Moreover, we expect to achieve small intestinal liquid collection as well as to recover all modules from the faecal matter of the included volunteers. We anticipate that the volunteers’ feelings about the ingestion and use of the medical device will be positive. To perform multi-omics analysis, we presume that the volume collected by the modules will be sufficient and that samples will be analysable to determine the functional potential of each sample. We expect to find differences in profiles depending on sample origins (faecal matter vs. small intestinal liquid). The bacterial composition is expected to be more diverse and richer in faecal samples compared to small intestinal samples according to the literature [23]. In a previous clinical investigation performed with a collection module, Shalon et al. showed distinct microbial communities depending on the collection site [44]. They notably found a higher abundance of *Pseudomonadota* in small intestinal samples than in faeces and a lower alpha diversity relative to the intra-individual diversity in intestinal samples compared to faeces. We also expect to observe differences in the metabolome. In the same clinical study, Shalon et al. analysed the bile acid profiles along the intestinal tract. As a result, they obtained divers bile acid compositions with more primary bile acids (Cholic acid and Chenodeoxycholic acid) in the small intestinal samples, and faeces were dominated by secondary bile acids [44]. The culturomics analysis will allow us to isolate microbes and potentially to identify new bacteria. These bacteria could possibly be new probiotics [45].

Pelican Health is proactively addressing the burden of faeces collection imposed on volunteers in the current study by ensuring that pick-ups align with the volunteers’ way of life in this study. Currently, we are developing approaches to facilitate both the recovery of faeces and the medical device recovery from faeces, thereby lowering additional costs and patient burden. 

Sample contamination is a common issue frequently observed during the employment of other non-invasive sampling tools [46], and even during catheter aspiration [18]. However, the design and technical constraints incorporated into the development of the Pelican Health sampling device are specifically intended to limit these situations. 

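### One pooled 12-of-15 rule lets the trial call safety demonstrated with related grade ≥3 adverse events in up to 3 of 15 healthy volunteers

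*Protocol article*

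**What the plan says.** Section 1.3 sets the aim: "The primary objective of this clinical study is to demonstrate the safety and performance of the medical device". It calls this objective composite and says that it "will be achieved if both the safety and the performance of the MD are observed for at least 12 out of 15 volunteers". Section 2.8 gives the same rule: the objective is "achieved if the safety and performance sub-criteria are met for at least 12 out of the 15 volunteers".

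Section 1.4 defines both components per volunteer and as yes/no.
- Safety is the "absence of the occurrence of adverse events of grade ≥3 with a proven or reasonably conceivable causal relationship with the MD", or with the procedure linked to it.
- For the other component, "Performance will be considered satisfactory if at least one of the three modules is analysable". A module is analysable if it is recovered within 96 hours, yields at least 25 µL and shows no faecal contamination.

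Four other provisions bear on the point.
- Section 2.8 plans an interim analysis of the safety component alone after the third volunteer.
- Safety of use is also a secondary objective, judged on the number and grade of adverse events and analysed descriptively (sections 1.3, 1.4 and 2.8).
- Section 2.7 sets 15 volunteers on feasibility grounds and replaces those with unusable data, up to 20 in total.
- Section 3 gives the expectation: "We predict that the medical device will be fully safe for the 15 volunteers".

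**The concern.** The rule counts volunteers who meet both components and does not ask why the others failed. A severe event attributable to the device costs the trial exactly as much as a late, low-volume or contaminated set of modules. Good sampling can therefore carry the trial past severe events: three such events with complete sampling in the other 12 volunteers give 12 of 15, and the objective is met.

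The objective is worded as a demonstration of safety, in the first evaluation of this device in volunteers, all of them healthy. If the rule is followed as written, the headline conclusion could say that safety was demonstrated when one exposed person in five had a related event of grade 3 or higher.

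**Working it through.** **Inputs**
- Threshold: 12 of 15 (sections 1.3 and 2.8).
- Safety failure: at least one related grade ≥3 adverse event in a volunteer (section 1.4).
- Performance failure: no analysable module (section 1.4).
- True risk of a related grade ≥3 event, q: not given. 10%, 20% and 30% are assumed for illustration.
- True performance rate, p: not given. 100% and 90% are assumed, independent of safety.

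The article gives no reference rate, error rate or power for this rule, so there is no stated calculation to reproduce. Its only figure is the threshold.

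**1. Largest number of safety failures compatible with success**

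15 − 12 = 3. If f volunteers without a safety failure fail on performance, at most 3 − f safety failures remain:

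| Performance failures in other volunteers | Safety failures still allowed |
|---|---|
| 0 | 3 |
| 1 | 2 |
| 2 | 1 |
| 3 | 0 |

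The maximum of 3 is reached only when the other 12 volunteers meet both components.

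**2. What the data could show at that maximum**

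3/15 = 20%. Exact (Clopper-Pearson) two-sided 95% intervals:

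| Volunteers with an event | Lower limit | Upper limit |
|---|---|---|
| 0/15 | 0% | 21.8% |
| 1/15 | 0.2% | 31.9% |
| 2/15 | 1.7% | 40.5% |
| 3/15 | 4.3% | 48.1% |

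For 0/15 the upper limit is 1 − 0.025^(1/15) = 21.8%.

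**3. Chance that the rule is met**

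A volunteer succeeds with probability s = (1 − q) × p, and the rule is met with probability P(X ≥ 12), X ~ Binomial(15, s).

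With p = 100% this equals P(at most 3 events):
- q = 10%: 0.2059 + 0.3432 + 0.2669 + 0.1285 = 0.944.
- q = 20%: 0.0352 + 0.1319 + 0.2309 + 0.2501 = 0.648.

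| True event risk q | p = 100% | p = 90% |
|---|---|---|
| 10% | 94.4% (s = 0.90) | 68.5% (s = 0.81) |
| 20% | 64.8% (s = 0.80) | 35.8% (s = 0.72) |
| 30% | 29.7% (s = 0.70) | 13.5% (s = 0.63) |

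**4. Do the other safety provisions change the rule?**

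The interim look covers three volunteers, and the article attaches no threshold or consequence to it. At a true risk of 20% it sees no event with probability 0.8³ = 51.2%. The secondary adverse event listing is descriptive. Neither enters the success criterion in section 2.8.

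**The case against.** The strongest reply is that this is a feasibility-sized pilot ("The number of subjects to be included is set at 15 healthy volunteers to meet practical feasibility requirements") with no hypothesis test attached to the primary rule, and that safety is watched elsewhere: in a safety-only interim analysis and in a stand-alone secondary objective. Stopping rules may well sit in the full protocol, which is not shown. All of this is fair and limits the practical effect. It does not alter the final criterion, which is stated twice and ties the word demonstrate to 12 of 15.

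A reader might infer more than the documents support in five ways.
- *That a risky device would pass with 94% or 65% probability whatever its sampling performance.* Those figures hold only if everyone without a safety failure also meets performance. Performance failures use up the same allowance and make the rule harder to meet.
- *That 12 of 15 may be met separately by each component, so that as few as 12 + 12 − 15 = 9 volunteers meet both.* This reading is strained. Section 1.3 calls the objective composite and asks for both components, and section 1.4 defines each per volunteer. The maximum of 3 safety failures is the same either way.
- *That the prediction in section 3 contradicts the rule or sets a zero-event bar.* An expectation is not a tolerance, and the text speaks of side-effects in general, not of grade ≥3 events. A zero-event bar would also be passed only 0.95^15 = 46.3% of the time at a true risk of 5%.
- *That a stricter threshold would settle safety.* With 15 volunteers, even no events leaves an upper limit of 21.8%.
- *That failing the trial on four performance failures is itself a fault.* Performance is half of the primary objective, so that outcome is intended.

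**Conclusion.** The point holds as a weakness in how the success rule is built. No figure is miscalculated and no passages contradict each other. Followed exactly, the plan would declare its objective of demonstrating safety achieved with related grade ≥3 events in up to 3 of 15 healthy volunteers. That maximum follows from the threshold alone and needs no assumption.

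The probabilities do rest on assumptions: a true event risk that the article does not give, independent volunteers, and a performance rate of 100% or 90%. Across those two rates the rule is met with probability 69% to 94% at a true risk of 10%, and 36% to 65% at 20%.

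One detail could widen the problem. Section 2.7 does not say whether an event in a replaced volunteer counts towards the safety component. If it does not, more than three exposed people could have such an event with the objective still met. The full protocol may answer this, so it is a reason for care in choosing the denominator and not a separate fault.

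**What to change.** Amend sections 1.3 and 2.8 as follows.
1. Apply the threshold of at least 12 of 15 to performance. If the composite is kept, use it only as a descriptor and state that both components must be met in the same volunteer.
2. Draw the safety conclusion separately, from the number of volunteers with a related grade ≥3 event among all who swallowed the device, including anyone replaced under section 2.7.
3. Report that number with its exact 95% upper limit, so that the reader sees how little even a clean result excludes.
4. Judge it against a safety criterion stated in advance. The limit is for the sponsor and clinicians to set.

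The cost is a stricter, less favourable safety statement and an amendment to the stated success rule in a study that already has ethics and regulatory approval and began recruiting in October 2022 (sections 2.3 and 2.9). No new data are needed. If the amendment is not practicable, reporting safety separately beside the existing rule, as in items 2 and 3, is the lighter course.
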